### Randomization and allocation concealment

2.6

Randomization sequence is generated using the Random Allocation Software (version 2.0), a validated online tool. Participants are allocated to groups in a 1:1 ratio using permuted blocks of size 4 (to ensure balanced group sizes). Allocation concealment is achieved using opaque, sealed envelopes labeled with sequential participant numbers; envelopes are opened by a researcher not involved in participant recruitment or outcome assessment after informed consent is obtained.

### Data collection and management

2.7

Data are collected by trained research assistants (blinded to group allocation) at baseline, post-intervention, and 4-week follow-up. Clinical data (BP, FBG, LDL-C) are recorded directly into a secure electronic database (EpiData 3.1). Blood samples are stored at −80 °C until batch analysis to ensure consistency. Dual independent data entry is performed to minimize errors; discrepancies are resolved by a third researcher. All data are anonymized (identified by participant ID only) and stored in a password-protected server at The Second People’s Hospital of Kunming. Data access is restricted to the study team, with the corresponding author responsible for data sharing (per reasonable requests from other researchers).

### Statistical analysis

2.8

The data analysis will be conducted using the Statistical Package for Social Sciences (SPSS) version 26. To ensure the accuracy of the data entry, it will be performed by two independent researchers who will cross-verify the input data for consistency. The baseline characteristics will be assessed using appropriated statistical tests based on the data distribution: independent *t*-tests for normally distributed data, Mann–Whitney *U* tests for non-parametric data, and Chi-square tests for categorical variables.

If the parameters meet the criteria for normal distribution, a repeated-measures ANOVA will be used to examine group × time interactions for primary and secondary outcomes. To account for multiple comparisons across the three co-primary outcomes (office BP, FBG, LDL-C), a Bonferroni correction will be applied, setting the significance level at *p* < 0.0167. Any two of these outcomes reach significance will be considered positive. Secondary outcomes will be analyzed descriptively and inferentially without correction, given their exploratory nature. To test the mechanistic hypothesis that ANS modulation and inflammatory/metabolic biomarkers mediate Lo-TENS’s effects on primary outcomes, we will conduct bootstrapped mediation analysis (5,000 resamples) using the PROCESS macro for SPSS 26. For each primary outcome (SBP, FBG, LDL-C), we will test whether the effect of Lo-TENS is mediated by pre-specified mechanistic markers (HF-HRV, norepinephrine, IL-6, and adiponectin), with 95% confidence intervals used to determine significant mediation. The magnitude of the effects will be quantified using partial eta-squared (*η_p_*^2^), with thresholds of 0.01, 0.06, and 0.14 indicating small, medium, and large effect sizes, respectively.

Subsequently, all analyses will be reiterated after the exclusion of drop-outs to conduct a per-protocol analysis.

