#### Eligibility criteria

2.2.1

Inclusion criteria: (1) Aged ≥60 years; (2) Diagnosis of multimorbidity, defined as co-occurrence of ≥2 of the following: EH (diagnosed per Chinese Guidelines for the Management of Hypertension (26)), T2DM (diagnosed per American Diabetes Association guidelines (27)), hyperlipidemia (diagnosed per Chinese Guidelines for the Management of Dyslipidemia in Adults (28)); (3) Medically stable, defined as no acute exacerbation of EH, T2DM, or hyperlipidemia in the past 3 months and no hospitalizations for cardiovascular/metabolic events (e.g., myocardial infarction, stroke, diabetic ketoacidosis) in the past 6 months; (4) Able to understand and comply with the intervention protocol (e.g., attend 4 weeks of TENS sessions); (5) Voluntary participation and signed informed consent.

Exclusion criteria: (1) Contraindications to TENS (e.g., pacemaker/implantable cardioverter-defibrillator, skin lesions at electrode sites, pregnancy); (2) Severe cognitive impairment (Mini-Mental State Examination score <24); (3) Severe comorbidities (e.g., end-stage renal disease, malignant tumors); (4) Use of other non-pharmacological interventions for cardiovascular/metabolic conditions (e.g., acupuncture, massage) within the past 1 month; (5) Unstable medication regimens for EH/T2DM/hyperlipidemia (e.g., dose changes within the past 2 months).

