### Sample size calculation

2.5

Sample size calculation is based on the primary outcome of FBG, using G*Power 3.1 software. A 2 × 3 analysis of variance (ANOVA) was selected for sample size calculation due to its suitability for assessing group (Lo-TENS vs. sham) × time (baseline, post-intervention, 4-week follow-up) interactions for continuous primary outcomes; mixed-effects models will be used for secondary analyses to account for potential missing data, consistent with modern pilot trial statistical practices. Based on prior Lo-TENS studies in T2DM (*f* = 0.282, the most conservative effect size) (20), *α* = 0.05, power = 0.80, and a 20% attrition rate, a total sample size of 50 participants (25 per group) is required. This sample size is appropriate for a pilot RCT to estimate effect sizes and assess feasibility.

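### The test for all three co-primaries depends on undefined normality criteria, and no test is named for an outcome that fails them

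*Protocol article*

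**What the plan says.** Section 2.8 (Statistical analysis) gives the primary test in one conditional sentence: "If the parameters meet the criteria for normal distribution, a repeated-measures ANOVA will be used to examine group × time interactions for primary and secondary outcomes". It does not say what the criteria are: which check, at what level, on raw values or residuals, pooled or by arm. It does not say what follows if they are not met.

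Two other methods are named, each for a different purpose:

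- Section 2.8 lists "Mann–Whitney *U* tests for non-parametric data, and Chi-square tests for categorical variables", but that sentence opens with "The baseline characteristics will be assessed using appropriated statistical tests based on the data distribution" and covers baseline comparisons only.
- Section 2.5 (Sample size calculation) says "mixed-effects models will be used for secondary analyses to account for potential missing data". That concerns missing data in secondary analyses, not non-normal primary outcomes.

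The decision rule carries no such condition. For the three co-primaries "a Bonferroni correction will be applied, setting the significance level at *p* < 0.0167", and "Any two of these outcomes reach significance will be considered positive". Section 2.5 adds "Sample size calculation is based on the primary outcome of FBG". Section 2.2.1 requires "Diagnosis of multimorbidity, defined as co-occurrence of ≥2 of the following" (hypertension, T2DM, hyperlipidemia), so a participant can qualify without T2DM.

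**The concern.** A significance threshold has a definite meaning only when attached to one defined test. For a co-primary that passes the normality check there is one, the group × time interaction. For a co-primary that fails there is none, although its result still counts towards the two-of-three rule. The analyst must then choose after seeing the data, among candidates that answer different questions: ANOVA on logs, a rank test on week-4 values, or a rank test on change. A borderline co-primary, and with it the overall verdict, could turn on that choice.

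The gap is the same for SBP, FBG and LDL-C. FBG is the sharpest case because the trial was sized on it, and a sample with and without T2DM may well look skewed or two-humped.

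**Working it through.** **1. The plan's own figure.** 0.05 / 3 = 0.0167, so the per-outcome threshold reproduces. The total of 50 participants does not bear on this point.

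**2. The branches side by side.**

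| Situation | Test named for a co-primary |
|---|---|
| Normality criteria met | Group × time repeated-measures ANOVA at 0.0167 |
| Criteria not met | None |
| Baseline characteristics not normal | Mann–Whitney (not an outcome test) |
| Secondary analyses, missing data | Mixed-effects model (not the primary test) |

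**3. How often might FBG fail?** The article gives no mean, SD, skewness or T2DM share for FBG, so every input here is an assumption: Shapiro–Wilk at 0.05, 20 to 25 per arm, failure at one or more of three visits with arms pooled.

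| Assumed FBG distribution | Trials failing |
|---|---|
| Mixture (T2DM mean 8 mmol/L, CV 25%; others 5.5, CV 9%), 40–60% T2DM | about 99% |
| Same mixture, 80% T2DM | about 88–96% |
| Same, all T2DM | about 65–75% |
| Single lognormal, CV 0.25 (20 per arm) | 65–70% |
| Single lognormal, CV 0.15 (20 per arm) | 36–39% |
| Exactly normal data (20 per arm) | 15% |

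**4. Does the ANOVA need the protection?** With lognormal outcomes, CV 0.15 to 0.45, within-person correlation 0.5 to 0.7 and 20 completers per arm, the raw-scale ANOVA rejected at 0.012–0.020 under no effect, against a nominal 0.0167. At equal arm sizes this amount of skew does not break it.

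**5. What does the open choice do to one outcome?** Under the mixture in step 3, with no effect:

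- A normality check followed by one fixed fallback (log ANOVA, Mann–Whitney at week 4, or Mann–Whitney on change) rejects at 0.011–0.019, which is nominal.
- Taking whichever of the three fallbacks is most favourable gives about 0.035–0.044, or 0.035/0.0167 = 2.1 to 0.044/0.0167 = 2.6 times nominal. This is a ceiling.
- With a 15% week-4 FBG reduction in T2DM participants (half of that at week 8), the three fallbacks disagree on significance in roughly 14–51% of simulated trials, depending on the T2DM share.

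**6. What does it do to the trial verdict?** With independent outcomes and no effect, the chance of at least two of three at 0.0167 is 3(0.0167²)(0.9833) + 0.0167³ = 0.0008. If FBG alone is inflated to 0.043, it is 0.0167² + 2(0.0167)(0.043)(0.9833) = 0.0017. At correlation 0.5 the change is 0.005 to 0.008, and at 0.8 it is 0.011 to 0.016. Under any dependence it cannot exceed (0.0167 + 0.0167 + 0.043)/2 = 0.038.

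**7. What if FBG were left untested?** Let SBP and LDL-C each have an assumed power of 0.65, be independent, and let FBG have power q. The chance of success is 0.65² + 2(0.65)(0.35)q = 0.4225 + 0.455q, against 0.4225 without FBG.

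- q = 0.65 gives 0.72.
- q = 0.17 to 0.28, the FBG power simulated at 20 per arm with 60% T2DM, gives 0.50 to 0.55.

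The loss is therefore about 0.08 to 0.13 with the simulated FBG power, not 0.30.

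**8. Is a fixed model a reasonable replacement?** Under the same mixture and 15% effect, a week-4 model adjusted for baseline and diabetes status raised power at 0.0167 from 0.21 to 0.31 (60% T2DM) and from 0.33 to about 0.51 (80% T2DM) against the raw ANOVA. Results were similar on the raw and log scales, with null rates of 0.015–0.021. The simulated effect peaks at week 4 and occurs only in T2DM participants, which favours this model, so the size of the gain is illustrative.

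**The case against.** The strongest reply is that a journal article condenses, and the handling of non-normal data is the kind of detail a statistical analysis plan would carry. Section 2.5 also names the group × time ANOVA for continuous primary outcomes without any condition. This stands in part: a missing fallback alone would not be a finding. But the article itself makes the primary test depend on the data and ties a fixed threshold and a success rule to it. That is a stated rule, and it can be judged as stated.

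Two mitigating points also stand. Section 2.3.3 blinds the data analysts, which limits choosing in a favoured direction, though it does not settle which test applies. The trial is a pilot whose first aims are feasibility and effect-size estimation, though it still sets a rule for calling itself positive.

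Several stronger readings might be inferred, and the documents do not support them:

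- *FBG is certain to fail the check.* No FBG distribution is given, and under one reasonable assumption failure is below 50%.
- *The false-positive rate more than doubles.* That needs the smallest of three p-values to be picked, which nothing in the article suggests. One fallback keeps the level.
- *The success probability falls from 0.72 to 0.42.* This assumes FBG is dropped altogether and would otherwise have had 65% power, far above the simulated 0.17–0.28.
- *The check is applied to raw values instead of residuals.* The text does not say which is meant.

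**Conclusion.** The point holds as a defect of specification. For any co-primary that misses undefined normality criteria, section 2.8 leaves the deciding test unnamed while still counting its result. This applies to all three outcomes and is most likely to matter for FBG.

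The harm is discretion rather than demonstrated error. The per-outcome rate stays near 0.0167 if a single fallback is used and reaches about 0.04 only at worst. The false-positive rate of the two-of-three verdict stays low, at 0.016 or less in the scenarios examined. What is exposed is a borderline result, since plausible fallbacks often disagree when there is a real effect. All the simulated figures rest on assumed FBG distributions. The reading of the text does not.

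Because the ANOVA holds its level under this skew, the condition brings no benefit to set against that discretion. It should be removed.

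**What to change.** In section 2.8, delete the conditional clause that opens the sentence on repeated-measures ANOVA. State instead that each co-primary is tested at p < 0.0167 with one model, fixed before unblinding and used whatever a normality check shows: the between-group difference at week 4, adjusted for the baseline value and, for FBG, for diabetes status. This also matches the Abstract, which places the co-primaries at post-intervention.

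Add that residual checks are diagnostic only. Name one sensitivity analysis, for example FBG on the log scale or a permutation p-value from the same model, and say that it cannot replace the primary result in the two-of-three rule. Making the log scale primary for FBG is optional. The essential step is to commit to one model.

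The cost is a few sentences, with no new data or participants. The week-8 measurements move to a secondary contrast.

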**Methods:**

A pilot single-center, single-blinded, sham-controlled RCT will enroll 50 older adults (≥60 years) with multimorbidity (≥2 of EH, T2DM, hyperlipidemia). Participants will be randomly allocated (1,1) to receive Lo-TENS (2 Hz, 30 min/day, 5 days/week for 4 weeks) plus routine care or sham Lo-TENS plus routine care. Co-primary outcomes are office systolic blood pressure (SBP), fasting blood glucose (FBG), and low-density lipoprotein cholesterol (LDL-C) at post-intervention. Secondary outcomes include 24-h ambulatory BP, heart rate variability (HRV), inflammatory/metabolic biomarkers, and quality of life. Mechanistic analyses will explore mediation by ANS and inflammatory markers. Follow-up assessments will be conducted 4 weeks post-intervention.

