However, no pilot randomized controlled trial (RCT) has yet investigated Lo-TENS for common multimorbidity in older adults, nor explored its mechanistic pathways through ANS and inflammatory/metabolic biomarkers. Low-frequency transcutaneous electrical nerve stimulation (Lo-TENS; ≤10 Hz) is a non-invasive, low-risk intervention that modulates ANS activity by stimulating peripheral nerves (14). Prior studies have shown that Lo-TENS reduces sympathetic tone (measured via plasma norepinephrine levels and HRV) and improves clinical outcomes in patients with single chronic conditions, such as EH and T2DM (15–17) For example, Stein et al. demonstrated that 2 Hz Lo-TENS robustly reduces sympathetic activity and increases parasympathetic tone in healthy adults (15), and subsequent studies have validated these effects in older adults with cardiovascular conditions (18, 19). A recent randomized trial in patients with type 2 diabetes further suggested that TENS may improve glycemic variability, although its effect on HbA1c remains inconclusive, warranting further mechanistic investigation (20).

A pilot RCT is critical for this research question to assess feasibility (e.g., recruitment, intervention adherence, attrition) and estimate effect sizes for a subsequent definitive trial (21). As an pilot RCT, this study first aims to assess the feasibility of Lo-TENS delivery in older adults with multimorbidity and estimate effect sizes for a subsequent definitive trial. Second, we examine the efficacy of Lo-TENS as an adjunct to routine clinical management for improving blood pressure, glycemic control, and lipid profiles in older adults with common multimorbidity (≥2 of EH, T2DM, hyperlipidemia). Third, we explore the underlying mechanisms of Lo-TENS by testing whether changes in ANS function (HRV, norepinephrine) and inflammatory/metabolic biomarkers (IL-6, adiponectin, FGF21) mediate its effects on clinical outcomes (22, 23).

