### Outcomes

2.4

All outcomes are measured at baseline, post-intervention (week 4), and 4-week follow-up (week 8) (Table 2).

**Table 2 tab2:** Timeline for participants’ enrolment, interventions, and assessments.

Time point	Study period							
	Enrolment	Allocation	Intervention					Close-out (follow-up)
	1 week before	0	1st week	2nd week	3rd week	4th week	Post-intervention	8th week
ENROLMENT								
Eligibility screen	X							
Informed consent	X							
Randomization		X						
INTERVENTIONS:								
Lo-TENS + routine clinical management								
Sham stimulation + routine clinical management								
ASSESSMENTS:								
24-h ABPM	X						X	X
FBG	X						X	X
TC	X						X	X
TG	X						X	X
Plasma glucose	X						X	X
HbA1c	X						X	X
HDL	X						X	X
LDL	X						X	X
LDL-cholesterol	X						X	X
24-h dynamic ECG	X						X	X
CRP	X						X	X
Adiponectin	X						X	X
TNF-α	X						X	X
FGF21	X						X	X
Norepinephrine	X						X	X

ABPM, ambulatory blood pressure monitor (the average, standard deviation, maximum and minimum values of patient’s daytime, nighttime, and all-day systolic, diastolic blood pressure, mean arterial pressure, and pulse pressure); CRP, C-reactive protein; ECG, electrocardiogram; FBG, fasting blood glucose; FGF21, fibroblast growth factor 21; HbA1c, glycosylated hemoglobin; HDL, high-density lipoprotein cholesterol; LDL, low-density lipoprotein; LDL-cholesterol, low-density lipoprotein cholesterol; TC, total cholesterol; TG, triglyceride; TNF-α, tumor necrosis factor-α.

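### The co-primary outcomes are set at week 4, but sizing, success and effect size rest on a three-visit group × time interaction that is not specific to week 4

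*Protocol article*

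**What the plan says.** - **Endpoint.** The abstract (Methods) states: "Co-primary outcomes are office systolic blood pressure (SBP), fasting blood glucose (FBG), and low-density lipoprotein cholesterol (LDL-C) at post-intervention". Section 2.4 places post-intervention at week 4 and measures every outcome at baseline, week 4 and week 8. Section 2.4.1 lists the primary outcomes without a time point.
- **Sizing.** Section 2.5 chooses a 2 × 3 ANOVA because it suits "group (Lo-TENS vs. sham) × time (baseline, post-intervention, 4-week follow-up) interactions for continuous primary outcomes". The inputs are f = 0.282, alpha 0.05, power 0.80 and 20% attrition, giving 50 participants. Mixed-effects models are kept for secondary analyses.
- **Test and success rule.** Section 2.8, for normally distributed data: "a repeated-measures ANOVA will be used to examine group × time interactions for primary and secondary outcomes". Each co-primary is judged at p < 0.0167, and significance on any two makes the result positive. No week-4 contrast and no required direction are given.
- **Effect measure.** Section 2.8: "The magnitude of the effects will be quantified using partial eta-squared", with cuts of 0.01, 0.06 and 0.14 for small, medium and large. Confidence intervals are mentioned only for the mediation analysis.
- **Aim.** The Introduction gives as part of the pilot's first aim to "estimate effect sizes for a subsequent definitive trial".

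**The concern.** The declared endpoint is the arm difference at one visit. The planned test asks whether the arm difference varies in any way across three visits, with baseline treated as one of the responses. With two arms and three visits it has (2−1)(3−1) = 2 numerator degrees of freedom. Because the success rule uses its p-value, an outcome can count towards a positive trial with no effect at the declared time point. In some patterns a real week-4 effect is also detected less often than by a test aimed at it.

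The effect measure raises a second problem. A definitive trial is normally sized from a difference in mmHg or mmol/L, an SD and a baseline correlation. Partial eta-squared from a 2-df test gives none of these.

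**Working it through.** **1. The plan's own figure.** For the within-between interaction, λ = f²·N·3/(1−ρ) with df 2 and 2(N−2), where ρ is the correlation between visits and sphericity is assumed. With f² = 0.282² = 0.0795, alpha 0.05 and power 0.80:

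| ρ | completers | enrolled, N/0.8 |
|---|---|---|
| 0 | 42 | 53 (51 if 42 × 1.2) |
| 0.1 | 38 | 48 |
| 0.5 | 22 | 28 |

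The protocol does not state ρ. The stated 50 is reachable with ρ of about 0 to 0.1, so it cannot be called wrong.

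**2. What f = 0.282 implies for week 4.** If δ is the arm difference at each visit in SD units, f² = Σ(δ − mean δ)²/12. Scaling each pattern to f = 0.282:

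| pattern (baseline, week 4, week 8) | week-4 difference | week-8 difference |
|---|---|---|
| week 8 only | 0 | 1.20 SD |
| doubling by week 8 | 0.69 SD | 1.38 SD |
| week 4 only | 1.20 SD | 0 |
| sustained | 1.20 SD | 1.20 SD |
| halving by week 8 | 1.38 SD | 0.69 SD |

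The design effect size therefore does not fix a week-4 effect.

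**3. Behaviour at the analysis threshold.** From the protocol: alpha 0.0167, and 50 × 0.8 = 40 completers. Assumed, because the protocol gives no values: a 0.8 SD effect, equal correlation between visits, ρ from 0.5 to 0.8.

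- Interaction: λ = f²·40·3/(1−ρ), df 2 and 76. Halving pattern (0, 0.8, 0.4): f² = 0.32/12 = 0.0267. Sustained, week-4-only and week-8-only patterns all give f² = 0.4267/12 = 0.0356.
- Week-4 ANCOVA: λ = d²·40/(4(1−ρ²)), df 1 and 37.
- Example at ρ = 0.5: λ = 0.0267 × 120/0.5 = 6.4 (halving); 0.0356 × 120/0.5 = 8.53 (the other three); ANCOVA 0.64 × 40/(4 × 0.75) = 8.53.

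| Probability of p < 0.0167 | ρ 0.5 | ρ 0.6 | ρ 0.7 | ρ 0.8 |
|---|---|---|---|---|
| Interaction, 0.8 SD at week 8 only | 56% | 69% | 83% | 96% |
| Interaction, 0.8 SD at week 4, sustained | 56% | 69% | 83% | 96% |
| Interaction, 0.8 SD at week 4, halving | 42% | 53% | 69% | 88% |
| ANCOVA, 0.8 SD at week 4 | 66% | 74% | 84% | 95% |

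The first two rows are identical: the test does not distinguish the declared effect from a purely delayed one. A simulation (20,000 trials, 20 per arm, 0.7 SD at week 8 only) agrees. At 0.0167 the interaction was significant in 43% (ρ 0.5) to 70% (ρ 0.7) of trials, while week-4 ANCOVA stayed at 1.6% to 1.7%.

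**4. Partial eta-squared.** With no effect at any visit and df 2 and 76, it follows Beta(1, 38). Its mean is 1/39 = 0.026, above the 0.01 cut for small. P(> 0.01) = 0.99³⁸ = 68%, and P(> 0.06) = 0.94³⁸ = 9.5%. In the simulation (ρ 0.5) its mean was 0.10 whether the 0.7 SD effect lay at week 4 only, at week 8 only or at both.

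**The case against.** The week-4 time point is attached to the co-primaries only in the abstract. In the body, sections 2.5 and 2.8 use the same interaction, so sizing and analysis agree in the kind of test. That is true, but no section names another primary time point, and the two statements still need reconciling.

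A reader might infer several stronger things that the documents do not support:

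- **That the interaction misses the week-4 effect.** It does not; a week-4 difference feeds into it.
- **That it always loses power.** The loss depends on pattern and correlation. With a sustained effect the gap at ρ 0.7 is about 1 point (83% against 84%), and at ρ 0.8 the interaction is slightly ahead (96% against 95%).
- **That the test inflates type I error.** With no effect at any visit it keeps its nominal level. A week-8-only effect is a real difference, though not the declared one, and nothing in the protocol suggests that such a pattern is likely.
- **That 56% to 83% is the chance of a positive trial.** It is per outcome. Success needs two of three, and the trial-level figure depends on how the outcomes are correlated.
- **That lack of direction is peculiar to this test.** A two-sided ANCOVA also rejects when sham does better. The remedy is a stated direction in the success rule.
- **That the pilot's effect estimate would be unusable.** The protocol does not exclude arm means and SDs by visit, and no decision uses the eta-squared cuts.

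A fuller plan might add a week-4 contrast. The point does not rest on that silence: the article itself names the test, threshold, success rule and effect measure. Treating baseline as a repeated response is also valid under randomisation, so baseline adjustment is recommended for efficiency.

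**Conclusion.** The concern holds in this form: the abstract declares a week-4 endpoint, while sizing and the success rule use a three-visit interaction that is not specific to week 4. Followed as written, the plan can credit an outcome with no effect at the declared time point. In the assumed week-8-only case with 0.8 SD, 40 completers and ρ 0.5 to 0.7, this happens 56% to 83% of the time per outcome. The cost in power for a true week-4 effect runs from about 24 points (halving effect, ρ 0.5: 42% against 66%) to none or a slight gain (sustained effect, ρ 0.8). Partial eta-squared alone is a poor input for the definitive trial because it has no sign, unit or time point and is above the protocol's small cut on average when nothing is happening. The effect sizes and correlations are assumptions. The mismatch in the text does not depend on them.

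**What to change.** - **Sections 2.4.1 and 2.8:** name week 4 as the primary time point. For each co-primary, make the primary test the between-arm difference at week 4 adjusted for the baseline value, by ANCOVA or as the week-4 contrast of a mixed model. State that success requires a difference favouring Lo-TENS.
- **Effect estimate:** report the adjusted mean difference with its 95% CI in mmHg or mmol/L, the SD, and the baseline to week-4 correlation. If partial eta-squared is kept, label it descriptive only.
- **Secondary:** week 8 and the overall interaction.
- **Section 2.5:** restate the sample size basis for the week-4 contrast, with its assumed difference, SD and correlation. As an illustration, n per arm = 2(1−ρ²)(z₁₋α/₂ + z₀.₈)²/d², a normal approximation that is slightly optimistic at this size. At alpha 0.0167, 0.7 SD needs 66 completers (83 enrolled) at ρ 0.5 and 44 (55 enrolled) at ρ 0.7. The authors may keep 50 on feasibility grounds, but should then say what week-4 difference it can detect.

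The cost is small. It is wording only, all measurements are already scheduled and SPSS 26 fits these models. The interaction loses its primary role and the sample size justification must be rewritten. The change should be made before any unblinded data are seen.

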#### Primary outcomes

2.4.1

Office blood pressure: Systolic blood pressure (SBP) and diastolic blood pressure (DBP) will be measured using a validated electronic sphygmomanometer (Omron HEM-7121) after 5 min of rest; average of 3 measurements (1 min apart).

Fasting blood glucose (FBG): Venous blood sample (8-h fast) measured via enzymatic assay (Beckman Coulter AU5800).

Low-density lipoprotein cholesterol (LDL-C): Measured via direct enzymatic assay to ensure accuracy in participants with hypertriglyceridemia, a common comorbidity in this population; venous blood sample (8-h fast) analyzed using Beckman Coulter AU5800.

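### The two-of-three success rule leaves the blood pressure test undefined, sets no direction of effect, and uses Bonferroni where Holm would control the same familywise error with more power

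*Protocol article*

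**What the plan says.** Section 2.8 examines every primary and secondary outcome in the same way: "a repeated-measures ANOVA will be used to examine group × time interactions for primary and secondary outcomes". With two groups and three visits (section 2.5), that interaction is an F test with 2 numerator degrees of freedom. The section counts "three co-primary outcomes (office BP, FBG, LDL-C), a Bonferroni correction will be applied", at p < 0.0167 per outcome, and gives the success rule as "Any two of these outcomes reach significance will be considered positive".

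The blood pressure component is described in different ways:

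- Section 2.4.1, Primary outcomes: "Office blood pressure: Systolic blood pressure (SBP) and diastolic blood pressure (DBP) will be measured".
- Abstract, Methods: "Co-primary outcomes are office systolic blood pressure (SBP), fasting blood glucose (FBG), and low-density lipoprotein cholesterol (LDL-C) at post-intervention".
- Section 2.8, mediation analysis: the primary outcomes are given as SBP, FBG and LDL-C.
- Section 3.1: the hypothesis is that Lo-TENS lowers SBP, FBG and LDL-C relative to sham.

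**The concern.** One sentence decides whether the trial is reported as positive, so each term in it should have a single meaning before data are seen.

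- **Which pressure.** Nothing says whether office BP passes on SBP, on either pressure, or on both. Under the either-or reading there are four tests at a level set for three, and the pressure that counts could be picked afterwards.
- **Which direction and when.** Significance alone suffices. A 2-df interaction can be significant because sham did better, or because the groups part only at week 8. The abstract places the co-primaries at post-intervention and section 3.1 expects reductions.
- **Which error rate.** Section 2.8 does not say whether 5% is meant to protect the claim for each outcome or the single two-of-three claim. Bonferroni covers both, but a uniformly more powerful procedure covers both as well. In a trial of 50 that difference matters.

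**Working it through.** **Inputs.** From section 2.8: three co-primaries, p < 0.0167 each, success if two or more pass. From section 2.5: f = 0.282 for FBG, α = 0.05, power 0.80, 2 × 3 design. Assumed, because the article does not give them: the SBP–DBP test correlation, the correlation between outcomes, and the within-person correlation.

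**1. The plan's own figure.** 0.05/3 = 0.01667, so 0.0167 reproduces. Write a = 0.05/3. With three independent tests, the chance of any false claim is 1 − (1 − a)³ = 0.0492.

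**2. If either SBP or DBP could count.** These are two-sided tests on a bivariate normal pair, with BP taken as independent of FBG and LDL-C. Let b be the chance of a false BP finding.

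| SBP–DBP correlation | b | Any false claim, 1 − (1 − b)(1 − a)² | False two-of-three when FBG truly works, 1 − (1 − b)(1 − a) |
|---|---|---|---|
| 0 | 0.0331 | 0.0650 | 0.0492 |
| 0.5 | 0.0313 | 0.0633 | 0.0475 |
| 0.7 | 0.0291 | 0.0612 | 0.0453 |

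Whatever the correlation, the bounds are 4a = 0.0667 for any false claim and 3a = 0.05 for false two-of-three success. So the excess over 5% concerns separate per-outcome claims only. If SBP alone counts, there is no excess. If both pressures must pass, the rule is stricter.

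**3. Direction.** With no true effects, independent outcomes and a two-sided z test as a simplification, the rule is met with probability 3a²(1 − a) + a³ = 0.00082. In simulation it was met in 0.00083 of trials, and in 0.00021 two significant effects both favoured Lo-TENS. That is about a quarter of the trials called positive. The absolute figures are small; the point is that the rule does not tell benefit from harm.

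**4. Bonferroni against Holm.** For an outcome with the FBG effect I use the within–between interaction formula λ = f² × N × 3/(1 − ρ). N = 42 and ρ = 0 give λ = 0.282² × 42 × 3 = 10.02 with 2 and 80 df, which returns the planned power of 0.80 at 0.05. Power is then q = 0.710 at 0.025 and p = 0.654 at 0.0167. Let d = q − p = 0.056. Outcomes are independent.

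- Bonferroni, three real effects: 3p²(1 − p) + p³ = 0.723.
- Bonferroni, two real effects and one null: p² + 2p(1 − p)a = 0.435 (0.434 by simulation).
- Holm rejects at least two when the smallest p is ≤ 0.0167 and the next is ≤ 0.025. With three real effects: 3q²(1 − q) + q³ − [3d²(1 − q) + d³] = 0.793.
- Holm, two real effects and one null: the same calculation gives 0.511.
- With correlation 0.5 between outcomes and three real effects (chi-square approximation), the figures are about 0.69 and 0.74.

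**5. What the stricter level buys.** The worst case for a false two-of-three result is one outcome that truly works (taken as certain to pass) and two that do not:

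- Bonferroni: 1 − (1 − a)² = 0.0331.
- Holm: 1 − 0.975² = 0.0494.
- No correction: 1 − 0.95² = 0.0975.

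**The case against.** Four points can be made for the plan.

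- **SBP is the likely intent.** The abstract, the mediation text and the hypotheses all name SBP alone, and the count of three fits that. Section 2.4.1 may simply describe how both pressures are taken. A reader might infer that DBP is a settled fourth primary and that error control is already broken. The article does not support this: it never says that either pressure suffices, and even then the two-of-three rule holds 5%. What stands is an inconsistency between the section that defines the primary outcomes and the other places.
- **Two-sided tests are normally read against the stated hypothesis.** That is fair, and section 3.1 gives the direction. Nobody need suppose that the investigators mean to report harm as success. But the success sentence does not refer to the hypothesis, and a 2-df interaction has no single sign to read against it.
- **Bonferroni is valid, simple and prespecified.** All true. A reader might infer that requiring two of three on top of Bonferroni is a double correction that gains nothing. That is wrong: step 5 shows 3.3% against 4.9%, and 9.75% with no correction. Two-of-three is the definition of success, not a multiplicity adjustment. The Holm gain also rests on giving all outcomes the effect that section 2.5 assumes for FBG alone.
- **This is a pilot.** Feasibility and effect-size estimation come first, which lowers the stakes. Efficacy is nevertheless a stated aim, and section 2.8 chose to set a success rule.

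**Conclusion.** The point holds in this limited form. The BP component and the direction and timing of effect are left open in the rule that decides success, and both should be settled before unblinding. The either-or reading would raise a false BP finding from 1.67% to about 2.9% to 3.1% (correlation 0.7 to 0.5). Error over separate claims would be about 6.1% to 6.3% at those correlations, 6.5% if all tests are independent, and at most 6.7%. False two-of-three success would stay between 4.5% and 4.9%, with a bound of 5%.

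Bonferroni is conservative, not wrong. Holm rejects everything that Bonferroni rejects and keeps 5% familywise control for each outcome. It adds about 7 to 8 points of two-of-three power under independence (72% to 79%, or 43% to 51%), and about 5.5 points at correlation 0.5 with three real effects. These figures are for the planned F test.

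**What to change.** 1. In section 2.4.1, state that the BP co-primary is office SBP and list office DBP as secondary.
2. In section 2.8, test the between-group contrast in change from baseline to week 4 for each co-primary, and count an outcome only if that contrast favours Lo-TENS. The interaction over all three visits can stay as a supporting analysis.
3. Replace Bonferroni with Holm: smallest p against 0.0167, next against 0.025, last against 0.05. Define positive as at least two Holm rejections, each favouring Lo-TENS.

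**Cost.** A few sentences and no new data. DBP loses primary status. False two-of-three success when one outcome truly works rises from 3.3% to 4.9%, still under 5%. Because section 2.5 is built on the 2 × 3 interaction, its power statement should be rechecked for the week-4 contrast.
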